**Figure 1 Fig1:**
[figure not shown]
**Conceptual framework based on Andersen and Newman [**[42]**].**

### Descriptive statistics

Descriptive statistics of the parameters (Table 3) will be calculated according to their means, confidence intervals, and *p*-values reflecting the extent of difference between arms. Comparisons will be made at the start and endpoint of the program. Stata svy commands will be used to account for clustering with *F*-tests used to evaluate the significance of differences between groups. As costs are not normally distributed, significance of differences between components listed in Table 4 at the start and end of the program will be calculated using confidence intervals with bootstrapped standard errors.

**Table 3 Tab3:** **Variables to be tested**

Conceptual framework category	Parameter	Description
Demographic characteristics	Household size	Continuous variable (min = 2 people, max = 23 people in Gujarat and 32 in Uttar Pradesh)
	Child sex	Male =0, female =1
	Child age	Continuous variable (min =2 months, max =59 months)
Characteristics of the social structure	Mother’s education	No or primary education =0, primary education or above =1, secondary education or above =2, tertiary education or above =3
	Father’s education	No or primary education =0, primary education or above =1, secondary education or above =2, tertiary education or above =3
	Scheduled caste	Not a scheduled caste =0, scheduled caste =1
	Scheduled tribe	Not a scheduled tribe =0, scheduled tribe =1
	Other backwards caste	Not another backwards caste =0, other backwards caste =1
Caregiver knowledge	Knowledge about ORS	No knowledge =0, knowledge =1
	Knowledge about zinc	No knowledge =0, knowledge =1
Enabling factors	DAZT program	Initial survey, final survey
	Below poverty line card	No BPL card =0, BPL card =1
	Very poor	Any other wealth quintile =0, second wealth quintile =1
	Poor	Any other wealth quintile =0, third wealth quintile =1
	Less poor	Any other wealth quintile =0, fourth wealth quintile =1
	Least poor	Any other wealth quintile =0, fifth wealth quintile =1
Need factors	Duration of diarrhea	Continuous variable (min = 0 days, max = 15 days in Gujarat and 32 in Uttar Pradesh)
	Blood in the stool	No blood in the stool =0, Blood in the stool =1
Treatment seeking	Seek treatment outside of the home	No treatment sought outside of the home =0, treatment sought =1
Treatment given	Given ORS	No ORS =0, given ORS =1
	Given zinc	No zinc =0, given zinc =1

**Table 4 Tab4:** **Descriptive statistics about costs**

	Costs according to source of care and components according to outpatient, inpatient, and home care
Costs according to source of care	
Public source—facility care	PHC, government hospital, government dispensary
	Auxiliary nurse midwife, sub-center
Public source—community care	Anganwadi worker/center
	ASHA
Private source	Private doctor
	Nursing home/private hospital
	Mobile clinic
	Chemist
	Traditional healer
	Charitable hospital, NGO, trust
Cost components according to outpatient, inpatient, and home care	
Direct medical	Consultation
	Dispensing
	Purchase of zinc (tablets or syrup)
	Purchase of ORS (packets)
	Purchase of other drugs
	Special food purchased
	Admission/hospitalization
	Other costs
Direct nonmedical	Transportation (round trip)
Indirect costs	Wages lost

ASHA: Accredited Social Health Activist; NGO: Non-governmental organization; ORS: Oral rehydration salts; PHC: Primary health center.

### Costing

The cost of the DAZT program from 2011 to 2013 (Gujarat) and 2014 (Uttar Pradesh) will be calculated from the societal perspective according to Saving Newborn Lives guidelines and standard textbooks [20],[40],[43]. The societal perspective reflects the incremental costs incurred by implementing agencies, government providers, and households. Program costs will be divided into capital costs and recurrent costs, with data derived from program records, primary sources, and interviews with individuals responsible for implementation. Capital costs will be annualized and discounted according to a rate of 3% according to the standard rate for economic evaluation in International Health [44]. Consumer price indices from the International Monetary Fund (IMF) will be used to inflate costs to 2014. Costs will be converted to US$ using exchange rates from OANDA.com. Incremental government provider costs will be derived using reported estimates of time spent on the provision of diarrhea treatment services by public sector providers. Economic costs to caregivers for diarrhea treatment of the episodes in the last 2 weeks will be evaluated according to data collected through household questionnaire and consist of direct medical costs of treatment, direct non-medical costs (transportation), and indirect costs (wages lost by caregivers) [45]. No adjustments will be made to collected data to approximate opportunity costs.

### Health outcomes

In the standard cost-effectiveness calculation, health outcomes will be derived from incremental changes in coverage measured in cross-sectional household surveys and inputted into LiST. LiST will estimate the incremental number of lives saved from the study’s start to its completion. The years of life lost (YLL) component of disability-adjusted life years (DALYs) will be calculated using the standard formula from the Global Burden of Disease study [46]. A life expectancy estimate will be taken from WHO life tables representing the midpoint between 1–4 years old. A discount rate of 3% will be used in reference case calculations, and age weighting will not be used to be consistent with the Disease Control Priorities Project second edition (DCP2) [41]. Long-term sequelae such as acute cognitive and psychomotor development effects in young children, the effects of diarrhea on stunting [4], and obesity and related conditions that can occur later in life (cardiovascular disease and diabetes) [47] were not measured and will not be considered. The net-benefit regression approach will be limited to episodes averted as it is impossible to know the specific long-term health outcomes for individual patients. Limitations of drawing data from a single uncontrolled study are recognized [48], although cost-effectiveness analysis is often conducted on data from a single effectiveness study, and conditions in the study sites are not atypical of other relevant settings in low- and middle-income countries.

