**Methods/Design:**

This study evaluates the cost-effectiveness of DAZT program activities relative to status quo conditions existing before the study, comparing a Monte Carlo simulation method with net-benefit regression, discussing the strengths and weaknesses of each approach. A control group was not included in the ‘before and after’ study design as zinc has proven effectiveness for diarrhea treatment. Costs will be calculated using a societal perspective including program implementation and household out-of-pocket payments for care seeking, as well as estimates of wages lost. Outcomes will be measured in terms of episodes averted in net-benefit regression and in terms of the years of life lost component of disability-adjusted life years in the method based on Monte Carlo simulation. The Lives Saved Tool will be used to model anticipated changes in mortality over time and deaths averted based on incremental changes in coverage of oral rehydration salts and zinc. Data will derive from cross-sectional surveys at the start, midpoint, and endpoint of the program. In addition, Lives Saved Tool (LiST) projections will be used to define the reference case value for the ceiling ratio in terms of natural units.

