**Table 1 Tab1:** **Diarrhea Alleviation through Zinc and Oral Rehydration Therapy (DAZT) Program Summary**

Sectors	Program activities
Public sector	Micronutrient Initiative (MI)
State-level policy changes	• Permission to implement DAZT was formalized through Memorandums of Cooperation between MI and the state government, and MI and the Department of Health and Family Welfare of Gujarat
	• In Uttar Pradesh, less formal permission was obtained from the government
	• Commitment from the Department of Women and Child Development in Gujarat
	• Both states added zinc to their NRHM guidelines and essential drug lists
Programmatic planning	National Rural Health Mission (NRHM) Program Implementation Plans (PIPs) were changed to include the procurement of zinc and ORS
Training	Three levels of training were conducted including (1) district level supervisors, (2) Block level supervisors and health workers, and (3) ASHAs and AWWs. Trios, a Delhi-based agency, conducted training in Gujarat, and three NGOs conducted the training in UP
Supply	• Supply was provided by two pharmaceutical companies including Healthy Life Pharma and FDC limited assuming that the public sector would treat 10% to 15% of diarrhea cases
	• Kits contained two ORS sachets and 14 taste masked zinc tablets, a measuring cup, and an informational leaflet for caregivers
Procurement	• Healthy Life Pharma and FDC limited provided the first procurement of kits
	• In Gujarat, in phase 1 (2011), MI provided ORS and zinc and in phase 2 (2012), MI limited its provision to zinc only (government procured ORS)
	• In 2013, the state governments disbursed funds to all districts to purchase zinc
	• ANMs may have used supply procured from sources other than MI
Incentives	Incentives were delivered to ASHAs, AWWs, and ANMs at monthly meetings to increase attendance rates
Distribution	• Supplies were distributed from Healthy Life Pharma to district medical stores, to district hospitals or block offices/CHC/PHC, to HSC-ANMs and CDPOs, to ASHAs and AWWs
	• ANMs informed PHC block level supervisors about needs; supplies were redistributed from areas of surplus to areas of shortage
Monitoring and supervision	• Supportive supervisors and MI divisional coordinators provided supportive supervision at the district, block, sub-center, and village levels in the form of data validation and capacity building
	• These mechanisms complemented existing monitoring mechanisms of the public health system

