	• FHI staff attended monthly meetings, district coordinators spent a lot of time in the field working with new staff

Accredited Social Health Activists (ASHAs); Anganwadi Workers (AWWs); Auxiliary nurse midwives (ANM); Child development project officer (CDPO); Community health centers (CHC); Diarrhea Alleviation and Zinc Therapy (DAZT); FDC Limited pharmaceutical company (FDC); Health subcenter (HSC); Indian Academy of Pediatrics (IAP); Indian Medical Association (IMA); Information, education, communication (IEC); Micronutrient Initiative (MI); Non-governmental organizations (NGO); National Rural Health Mission (NRHM); Oral rehydration salts (ORS); Primary health centers (PHC); Program Implementation Plans (PIP); Rural medical providers (RMP); Short messaging service (SMS); Uttar Pradesh (UP).

The objective of this study is to evaluate the cost-effectiveness of the DAZT program under real-world conditions compared to the status quo existing before the intervention was introduced in the study area. Two analytical approaches will be used to meet this objective: calculation of cost-effectiveness using a Monte Carlo Simulation method with patient level data [20], and calculation of cost-effectiveness using a net-benefit regression approach to control for covariates [21].

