Policy recommendations from the completed research will add to the growing literature evaluating the cost-effectiveness of zinc for diarrhea treatment in low- and middle-income countries. Findings will be timely as India is developing a Health Technology Assessment (HTA) program in collaboration with the UK National Institute of Health and Care Excellence [34], in which the importance of CEA in policy making can be expected to increase. In addition, local capacity to produce zinc is rapidly expanding including Bharat Immunologicals and Biologicals Corporation Limited (BIBCOL), which is a government-owned corporation with the capacity to produce 240 million of 20 mg scored tablets of zinc sulfate per year [35]. Currently, about 40 private companies are producing zinc for local and international markets.

This article presents the DAZT program in India. Analytic methods for evaluating cost-effectiveness are described and compared, in addition to methods for assessing wealth quintile using principal components analysis. Strengths and limitations of the study are discussed, followed by arguments against targeting zinc according to subgroup, and considerations necessary for drawing conclusions about generalizability.

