Secular trends such as improvements in living conditions, access to safe water, and improved sanitation may have contributed to the decline in diarrhea prevalence in the DAZT study area [60]. However, secular trends may be less relevant for costs as economic growth is unlikely to drive prices for diarrhea treatment down. In addition, this study design is sensitive to sudden changes in the conditions of the study area [61]. The Hawthorne effect is a potential confounder, which would overstate the magnitude of the effect [48]. Regression towards the mean may be problematic [58], which means that if a study had high diarrhea prevalence at beginning, future measurements will be likely to be less extreme. The DAZT study found a 14% prevalence of diarrhea in 2011, while levels were 13% in 2005/6 in Gujarat [36] and were 9% nationwide [7]. Regression to the mean predicts that the prevalence would be lower in future surveys as downward changes would be more frequent than upward changes.

Limitations exist in that household data is based on self-report, reporting bias could have occurred, and long-term outcomes and programmatic outcomes such as quality are not measured. Some researchers argue that only children who receive the recommended 10–14 day course should be included in analysis. However, in the DAZT program, most children only received partial courses of zinc in addition to antibiotics and anti-diarrheal medications. Seasonal effects are possible given that each survey was given at a different point in the monsoon cycle across the years of the study. Limitations of principal components analysis are recognized, such as not evaluating the quality of assets, assuming the first principal component to be an adequate indicator of socioeconomic status, being a relative measure, and producing quintiles with variable arrays of asset ownership [53],[62],[63]. Finally, outcomes will not be evaluated according to severity, which could lead to outcomes such as children with fewer symptoms or shorter episodes having more favorable cost-effectiveness.

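### The LiST analysis credits the whole start-to-endpoint rise in ORS and zinc coverage to DAZT, and nothing tests partial attribution

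*Protocol article*

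**What the plan says.** Under Health outcomes, the protocol article states that "health outcomes will be derived from incremental changes in coverage measured in cross-sectional household surveys and inputted into LiST", and that "LiST will estimate the incremental number of lives saved from the study’s start to its completion". The abstract names the driver, saying that LiST will model "deaths averted based on incremental changes in coverage of oral rehydration salts and zinc".

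The objective at the end of the Background sets the comparator: the programme is assessed "compared to the status quo existing before the intervention was introduced in the study area". The abstract explains the design: "A control group was not included in the ‘before and after’ study design as zinc has proven effectiveness for diarrhea treatment".

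Strengths and limitations names secular trends among the biases of an uncontrolled before-and-after study. Where it develops the point, it considers better living conditions, water and sanitation as causes of lower diarrhea prevalence. It then says that "secular trends may be less relevant for costs as economic growth is unlikely to drive prices for diarrhea treatment down". Coverage of ORS or zinc is not mentioned there. The article describes no background coverage trend, external comparison series or alternative LiST counterfactual.

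**The concern.** The question is whether a delivery programme is cost-effective. Strengths and limitations itself says that equipoise lay in the delivery strategy and not in zinc. The quantity in doubt is therefore how much coverage growth the programme caused. A start-to-end increment against the pre-programme status quo sets that share at 100%. The defence offered for having no control group, that zinc works, supports the effect per treated child. It does not support attribution of the coverage rise.

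The article gives some reasons why coverage might have risen anyway. The Background describes a decade of efforts to introduce zinc and ORS and growing local zinc production: "Currently, about 40 private companies are producing zinc for local and international markets". The Discussion mentions a government oral rehydration programme. Table 1 notes that "ANMs may have used supply procured from sources other than MI".

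If part of the rise is not due to DAZT, deaths averted are too high and the ICER too low. The intervals and acceptability curves in the Monte Carlo section reflect resampling of household costs and outcomes and gamma draws for programme costs. They cannot show an attribution error.

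**Working it through.** The article gives no start or end coverage for the study districts, no LiST result and no ICER, so there is no stated figure to reproduce. Two things can be checked: the interval over which the rise is credited, and how sensitive the ICER is to the attributed share.

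**1. Interval (Table 2, survey midpoint to survey midpoint)**

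- Gujarat: 22 March–10 May 2011 to 28 September–18 November 2013. This is 922 days; 922 / 365.25 = 2.52 years.
- Uttar Pradesh: 1 April–21 June 2011 to 25 August–12 October 2014. This is 1,225.5 days; 1,225.5 / 365.25 = 3.36 years.

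Both exceed the 2 years of implementation given under Setting and study design.

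**2. Effect of the attributed share**

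Let E be the health effect that LiST gives for the full rise, and s the share of the rise not due to DAZT. Assume that the effect is proportional to the coverage increment. The programme effect is then (1 − s)E. With incremental costs fixed, the ICER is multiplied by 1 / (1 − s).

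| s (assumed) | Effect kept | ICER multiplier |
|---|---|---|
| 0% | 100% | 1.00 |
| 10% | 90% | 1 / 0.90 = 1.11 |
| 25% | 75% | 1 / 0.75 = 1.33 |
| 50% | 50% | 1 / 0.50 = 2.00 |

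**3. Costs need not stay fixed**

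The Costing section includes incremental government-provider and household costs. Split incremental cost into a part P that does not depend on s and a part V that scales with the attributed coverage. The multiplier becomes (P / (1 − s) + V) / (P + V). With P and P + V both positive, it is smaller than 1 / (1 − s) if V is positive, and larger if V is a net saving. Costs must therefore be recomputed together with the effect.

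**4. Break-even share**

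With costs fixed, a state's result still meets its threshold while s ≤ 1 − ICER / threshold. The thresholds in the Monte Carlo section are US$1,740 (Gujarat) and US$571 (Uttar Pradesh). An ICER at half the threshold tolerates s up to 50%; one at three quarters tolerates 25%.

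**5. What background growth could mean**

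For growth of g points a year over T years and a total rise of R points, s = gT / R. For Gujarat with g = 1 (assumed), s = 2.52 / R: 25% for R = 10, 13% for R = 20 and 8% for R = 30. With g = 0 there is no bias. Both g and R are assumptions, and the result depends heavily on them.

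**The case against.** The case against making much of this is substantial.

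- **Disclosure.** The abstract, Health outcomes, and Strengths and limitations all concede the weakness of an uncontrolled study, and the last names secular trends. The status quo is the declared comparator. An article may also leave LiST settings to a fuller plan. This stands, and it means that the gap is specific: the trend discussion omits coverage, and no analysis of attribution is described.
- **Thin evidence of background growth.** The sample size section says that very few children had received zinc before the programme. The Background puts national ORS coverage below 30% although ORS has been in wide use since the 1980s. Whatever the 2005–10 project achieved by 2010 is already in the start survey. Table 1 lists links to local manufacturers and state procurement changes as programme activities, so some of the other supply may be DAZT-induced. This stands: the documents make background growth plausible but do not demonstrate it.
- **Direction.** Activities began in late 2010 (Ethical approval and study status), before the start surveys of March to June 2011. Start coverage may already contain some programme effect, which would bias the other way. This also stands.

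A reader might infer three stronger points that the documents do not support.

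- **A larger bias in Uttar Pradesh because its interval is longer.** That follows only if the total rise is assumed equal in both states. If background growth r and programme effect p both accrue linearly, the share is rT / (rT + pT) = r / (r + p), and T cancels.
- **A threefold ICER.** This needs 2 points a year of background growth, a 10-point rise and fixed costs in Uttar Pradesh (s = 2 × 3.36 / 10 = 67%). It is a corner case on assumed inputs.
- **A pre-programme slope from the 2005/6 figure in the limitations text.** That figure is diarrhea prevalence in Gujarat, not ORS coverage.

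**Conclusion.** The point holds as a gap in the sensitivity analysis. The LiST calculation attributes the full coverage rise to DAZT, the stated defence concerns zinc's effectiveness, and neither the secular-trend discussion nor the simulated uncertainty reaches coverage.

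The size is unknown. The multipliers of 1.11 to 2.00 rest on assumed shares of 10% to 50%, on an effect proportional to the coverage increment, and on fixed costs. Net overstatement of deaths averted is the likelier direction but is not certain, because of the late start surveys. The general disclosures make this no reason to reject the design. They also do not tell a reader whether the cost-effectiveness conclusion would survive partial attribution.

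**What to change.** Under Health outcomes and the Monte Carlo section:

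1. Keep the pre-programme status quo as the reference case.
2. Add LiST sensitivity scenarios in which a stated share of the coverage rise, for example 0%, 10%, 25% and 50%, is not due to DAZT. Vary ORS and zinc separately, since zinc use started near zero and ORS use did not.
3. Recompute incremental costs consistently in each scenario, and report the ICER and acceptability curve for each.
4. State, for each state, the largest non-programme share at which the result still meets its GNI threshold.
5. Use an external pre-programme ORS slope only if comparable coverage data exist for these areas.

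In Strengths and limitations, extend the secular-trend paragraph to coverage, and note that activities preceded the start surveys.

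The cost is a few more model runs per state and a short text change, with no new field data. The downside is a possibly less favourable range of ICERs.

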### Cost-effectiveness analysis

Cost-effectiveness will be calculated using two different approaches including 1) Monte Carlo Simulation with patient level data [20] and 2) a net-benefit regression-based approach [21].

